### a. Justification for Conducting the Project:

#### (i) Health needs of the local community

As the global population ages, the growing prevalence of dementia has become a worldwide public health concern (1). Dementia, a progressive disorder, leads to deteriorating perceptual and cognitive abilities, behavioral changes, and loss of independence (2). Dementia impairs patients' social or occupational functioning and is a major cause of disability in older age. These symptoms not only impact the quality of life of people with dementia but also cause psychological distress for their caregivers (2,3). Currently, 50 million people live with dementia worldwide, which is predicted to rise to 82 million by 2030(4). An ongoing modelling study (5), which is part of a larger project named, "Tools to Inform Policy: Chinese Communities' Action in Response to Dementia (TIP-CARD)" shows that 178,139 people aged 60 years and older live with dementia in Hong Kong in 2021, and over 70% of dementia costs relate to informal care.

Dementia care largely rely on informal caregivers, such as family members, friends, and neighbors. These caregivers are vital partners in the health system and contribute to the realisation of healthy ageing and aging-in-place initiatives. In Hong Kong, over 62.6% of people with dementia have at least two informal caregivers (5). With input from multiple informal carers, the average informal care time amounts to 400 hours per month, 40% of which is attributed to managing behavioral and psychological symptoms of dementia and ensuring their safety (supervision time) (5).

Informal caregivers' physical and mental health are adversely affected by the demanding caregiving tasks they perform, leading to a higher level of psychological distress (6). The changing behaviors and functional dependence of people living with dementia require informal caregivers to spend longer hours and better cognitive preparedness for taking care of the patients, which may lead to a higher level of psychological distress (7). In Hong Kong, around 15.5% of dementia caregivers experienced burnout (6). Especially during the COVID-19 pandemic, 64.7% of people caring for someone with dementia reported suffering from probable depression and increased levels of anxiety and stress (8). The Chief Executive's 2022 Policy Address highlights enhancing support for caregivers and enhancing their mental well-being. However, very limited support is currently available for caregivers of people with dementia in the local community.

Considering the aforementioned features and impacts of caring for individuals with dementia, there is an urgent need for a self-instructed, flexible, and convenient intervention within the home environment to effectively enhance caregivers' psychological well-being in Hong Kong.

**(ii) What is the existing evidence before this project based on an up-to-date literature search?**

Evidence on interventions supporting dementia caregivers is limited and mainly restricted to Western countries. A recent large-scale systematic review on the effectiveness of dementia-related interventions in Chinese communities found very limited evidence about dementia caregivers among 525 included unique randomized control trials (RCTs) (9). Among the existing evidence, different types of interventions to reduce caregivers' stress and improve their psychological well-being have been studied, including case management, cognitive stimulation, cognitive and behavioral interventions, education, physical activity interventions, psychosocial support, relaxation and skill-building (10). Although most psychosocial interventions appear to be effective at reducing caregiver stress and psychological morbidity, treatment effect sizes have been small and inconsistent. Among these interventions, mindfulness-based interventions (MBIs) have been widely used to reduce psychological distress in dementia caregivers and show consistent and promising results (2).

Mindfulness refers to "the awareness that emerges through paying attention on purpose, in the present moment, and non-judgmentally to the unfolding of experience moment by moment" (11). Several recent systematic reviews provide robust evidence for the medium to large effect of MBIs on reducing caregivers' psychological distress, depression, burden, and enhancing quality of life by improving their ability to cater to the needs of people with dementia and managing daily stress and emotional challenges associated with caregiving (2,12), as well as enhancing relationship between caregivers and recipients (2).

Dementia caregivers bear significant daily caregiving responsibilities and dedicate the majority of their time to companionship and ensuring the safety of people with dementia. This responsibility often leaves caregivers with limited time and availability to engage in mindfulness practice outside of the home. However, the practice of mindfulness requires conscious effort and can be difficult to maintain in the home environment, especially for novice meditators who are already expending cognitive resources to control their self-regulatory skills (13). Beginning mindfulness practitioners commonly report easily being distracted during practice, fall asleep, wrestle with tiredness or ambivalence, difficulty of incorporating mindfulness practice into their daily life (14). The adoption of digital technology may support beginners' mindfulness practice, such as Web-based interventions (15) or smartphone apps (16) that can deliver guided audio-recorded mindfulness practice in facing the challenges of practicing and adhering to mindfulness (17). However, there are limitations with these audio-based MBIs, including a low adherence rate and the failure of participants to maintain these practices over the long term (17).

**(iii) How will this project add value to existing evidence in addressing the health needs of the local community?**

Virtual reality (VR) is an immersive technology that may boost the advantages of mindfulness meditation and facilitate participants' attention management. It refers to the use of a headset to create a 360-degree virtual environment, incorporating realistic 3D graphics, stereoscopic viewing, and head tracking (18). The use of VR technology with natural environments embedded in the system to assist mindfulness practice is supported by attention restoration theory (ART) (19). Natural stimuli in VR have the potential to reduce mental fatigue and increase attention (20). Additionally, nature can enhance ecological behavior, both in real-world and virtual experiences (21). The immersive nature of VR blocks distractions, allowing participants to focus solely on mindfulness practice (18).

VR-based mindfulness practice in a pleasant and immersive virtual environment may relieve physical and mental discomforts frequently experienced by beginning mindfulness practitioners without compromising their present-moment awareness (20). It also provides access to physically or cognitively inaccessible stimuli, enhancing guided imaginary mindfulness (21). Furthermore, VR also facilitates participants' application of mindfulness skills to real-life practice, and its non-traditional format may further increase their acceptance of the therapy (20).

VR-based MBI has recently been proposed as a medium to support mindfulness practice and become an effective way to improve participants' psychological well-being and cultivate spiritual experiences, especially strong feelings of awe (22). Specifically, compared to audio-based mindfulness, VR-based MBIs have been shown to offer several additional benefits, including improved well-being (23), higher treatment adherence (24), reductions in vigor, fatigue, and confusion (25) and more enjoyable experiences (26). However, VR-based mindfulness practice studies are predominantly conducted in a clinic environment or specific settings rather than a home environment (20). Practicing in home environment may enable participants to feel safe and remove their concerns about leaving the person with dementia. VR-based MBI practice can be time- and cost-efficient, simple to initiate and complete, and practical for caregivers at home.

Meanwhile, local evidence on VR-based interventions targeting psychological health issues such as depression, anxiety, and stress (27), alongside studies on the benefits of mindfulness for dementia caregivers' well-being (28) provides form a foundation for contemplating the integration of VR technology into mindfulness training programs. This collective body of research suggests a promising path for incorporating VR-based mindfulness practices for family caregivers for persons with dementia within the local context of Hong Kong.

**b. Aim and Objectives:**

This pilot study aims to explore the feasibility, acceptability and efficacy among dementia caregivers of the MBI delivered by VR technology (VR-based MBI) in the home environment. The specific research questions and hypotheses are as follows:

- **How do dementia caregivers perceive VR-based MBI?**

We will explore the feasibility, acceptability and understanding of using VR technology or audio to learn MBI among caregivers of people with dementia through a focus group qualitative study and a quantitative study using the Treatment Acceptability/adherence Scale. The readiness of caregivers to practice MBI at home after observing group sessions will also be explored.

- **Does the VR-based MBI offer additional benefits to psychological well-being compared with audio-based MBI and usual care?**

We will address this question through a 3-arm pilot randomized controlled trials (RCT). Using an 8-week audio-based MBI protocol and usual care as comparing conditions. We hypothesize that among caregivers of people with dementia:

**HP1:** The VR-based MBI group will show greater improvement in psychological well-being (**Primary Outcome**) than the audio-based MBI group, while the audio-based MBI group will show greater improvement than waitlist control group

Psychological well-being will be assessed through depression, anxiety and stress, as well as general wellbeing.

- **Does the VR-based MBI offer additional benefits to caregivers' mindfulness and quality of life, care recipients' quality of life and the relationship between caregiver and care recipient, compared with audio-based MBI and usual care?**

We will address this question through the RCT mentioned above. Compared with the audio-based MBI and usual care groups, we hypothesize that:

**HP2:** The VR-based MBI group will show greater improvements in caregiver burden, mindfulness level, and quality of life (**Secondary Outcomes**) than the audio-based MBI group, while the audio-based MBI group will show greater improvement than waitlist control group;

**HP3:** The relationship between VR-based MBI group caregivers and the care recipients (**Secondary Outcomes**) will show greater improvement than the audio-based MBI group, while the audio-based MBI group will show greater improvement than waitlist control group;

The proposed study will adopt the RE-AIM framework to plan interventions that had the potential to: (1) reach a high proportion of dementia caregivers, (2) effectively increase caregivers' psychological well-being and quality of life; (3) be scalable to improve potential adoption across care settings, (4) be implemented at a reasonable cost, and (5) lead to psychological well-being maintenance and be sustained in typical community settings.

c. **Project Plan:**

(i) **Target group**

Participants

Caregivers of persons with mild-to-moderate dementia.

Inclusion criteria:

- Aged 18 years or older;
- Primary informal caregivers who spend over four hours/day taking care of a community-dwelling person who has been clinically diagnosed with any type of mild-to-moderate dementia at least 6 months;
- Self-reported psychological distress
- Able to speak and read Cantonese.

Exclusion criteria:

- Have practiced mindfulness-based intervention for at least 3 months in the past;
- Have hearing or visual impairment that cannot practice mindfulness via wearing VR glasses embedded in a mobile phone app;
- Do not own a smart phone that can install the VR-based MBI app;
- Caring for a person with dementia living in a residential care setting;
- Caring a person with severe level of dementia;
- Have been diagnosed with any mental disorder or on-site of psychotic disorders;
- Receiving any other type of mental health intervention;
- Participants with a history of motion sickness (due to the risk of VR triggering motion sickness)
- Unable to understand Cantonese.

We propose a sample size of 90 participants for our three-arm RCT pilot study, with 30 participants in each arm, to ensure adequate distribution and feasibility while minimizing costs. This size allows us to gather preliminary data and insights into trial logistics, as well as sufficient qualitative feedback through focus group discussions. Additionally, this sample size supports our ability to estimate potential effect sizes (from 0.4 to 0.54) identified from previous studies (22,24), refine hypotheses, and inform the design of a larger trial.

Given that over 178,139 residents live with dementia in Hong Kong (5), we anticipate that it will be feasible to identify and recruit 90 older adults with dementia and their respective caregivers. To improve **Reach**, we will leverage our established network comprising local dementia care facilities, support groups, and community organizations. Building upon prior engagements with dementia caregivers, such as past participants, we aim to employ targeted outreach methods. These will encompass online platforms, posters and community events, to raise awareness and facilitate participant identification.

**(ii) Implementation plan**

Design

This proposed study will be a pilot RCT to examine the feasibility, acceptability and potential effectiveness of implementing the intervention with caregivers of people with dementia. Ethics approval will be obtained from the Office of Research and Knowledge Transfer, Lingnan University and HKU/HA HKW Institutional Review Board (HKU/HA HKW IRB).

Setting

Participants will practice MBI at their home. For enhancing the **adoption**, we will collaborate with local dementia care facilities and support groups and engage key stakeholders by highlighting the potential benefits of the intervention and demonstrate the feasibility and relevance of the intervention. Regular communication will be conducted to ensure a smooth adoption process.

Specifically, participants will be recruited through (a) three District Elderly Community Centers (DECCs) participating in the Dementia Community Support Scheme (DCSS), (b) participants of a previous dementia study, and (c) open recruitment from community service centers and other health and social care facilities.

First, three DECCs in the Tuen Mun area, who are DCSS partners, will serve as the main recruitment sites for the proposed. The Hong Kong SAR Government has launched the DCSS to provide multi-disciplinary community support services through medical-social collaboration for people with mild or moderate dementia and family carers since 2017 (The Government of the Hong Kong SAR, 2018, July 4). Apart from DCSS, the three DCSS-partner DECCs also provide other support and services for caregivers of people with mild-to-moderate dementia. Currently, around 330 caregivers of people with dementia are registered service users.

Second, we will contact participants (i.e., dementia caregiver) of our previous TIP-CARD study. In TIP-CARD project, 750 participants of the survey in 2021-2022 have already consented to being contacted for other dementia-related projects.

Third, when necessary, we will also conduct open recruitment. We will distribute our recruitment poster to older adults via community care facilities (e.g., DECC, NEC, and other community care centres) and mass email to participants in a community service project (n>500) for which the PA serves as project manager.

### Procedures

The pilot RCT is a 3-arm, parallel, single-blinded trial to examine the feasibility, acceptability and potential effectiveness of the VR-based MBI, following the “Consolidated Standards of Reporting Trials” (CONSORT) guidelines(29). The intervention will last eight weeks with assessment periods at baseline, posttreatment, and 2-months follow-up. We will also conduct focus group for the intervention group after the intervention and at follow-up, using an interview guide. A consort diagram of procedures for our RCT pilot design and RE-AIM considerations is shown in Figure 1.

Figure 1. Consort diagram of procedures for randomised controlled trial design and RE-AIM considerations

[figure not shown]

### Randomisation

Eligible participants will be randomly assigned into three groups: A) VR-based MBI (Intervention group) B) audio-based MBI group (control group) and C) Usual care group (Waitlist control group). Individual randomization using serially numbered opaque sealed envelopes (SNOSE) will be used to ensure that the allocation sequence is concealed from participants before the group allocation. The PA will prepare about 90 identical, opaque, sealed A5-sized envelopes, with a unique three-digit serial number on the cover of each envelope as an identifier. One-third of the envelopes will contain the action plan for the intervention group, another third the action plan for the audio-based MBI group, and the remaining envelopes the action plan for the waitlist control group. The intervention materials will be inserted into the envelopes, which will be sealed, shuffled, and numbered. Once a participant consents to participate in the study, the RA will open one envelope according to the sequence of the serial number and assign the participant to a treatment condition based on the action plan. No participants will be blinded to the given interventions.

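### Allocation is drawn from a shuffled closed pool of about 90 envelopes, a third per arm, that matches the target of 90, so an RA who keeps count can partly predict the last assignments

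*Protocol*

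**What the plan says.** The sample size paragraph (Project Plan, Target group) fixes the total and the split: "We propose a sample size of 90 participants for our three-arm RCT pilot study, with 30 participants in each arm".

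The Randomisation section then describes the mechanism:

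- Pool: "The PA will prepare about 90 identical, opaque, sealed A5-sized envelopes, with a unique three-digit serial number".
- Composition: "One-third of the envelopes will contain the action plan for the intervention group, another third the action plan for the audio-based MBI group". The last third is for the waitlist arm.
- Order: "The intervention materials will be inserted into the envelopes, which will be sealed, shuffled, and numbered".
- Use: after consent, "the RA will open one envelope according to the sequence of the serial number and assign the participant to a treatment condition".

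The section says the sequence is hidden from participants before allocation. It does not say the same of the staff who enrol. It describes no computer-generated list and no independent holder of the sequence. On blinding it says "No participants will be blinded to the given interventions". The Procedures section calls the trial single-blinded, and the Blinding section explains that the RA collecting post-test data is the blinded party.

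**The concern.** Concealment has to stop the people who enrol from knowing, or guessing well, what the next assignment will be. The protocol publishes the composition of the pool, sizes the pool to match the target, and has one person open the envelopes in order. That person can subtract the results so far from 30 per arm and see what is left. Near the end the remaining envelopes become informative, and if the pool is used up the last one is certain.

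If someone with that knowledge influenced whom to approach or when to enrol, keener or more distressed caregivers could be directed towards or away from an expected arm. The primary outcomes (DASS-21 and ONS4) are reported by caregivers who know their arm, so differences in expectation or distress at entry would feed into the comparison of VR with audio and waitlist. The pilot also states efficacy hypotheses and is meant to inform effect sizes for a larger trial, which might inherit the same procedure.

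**Working it through.** **Inputs.** 90 participants and 30 per arm (Target group section); about 90 envelopes in thirds (Randomisation section). The plan's own figures agree: 90 / 3 = 30. Assumptions for the main case: the pool is exactly 90, all are used, the shuffle is perfect, and someone keeps a tally.

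**1. Certain assignments.** The k-th assignment from the end is certain when the last k envelopes all hold the same arm:

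P(k) = 3 × C(30,k) / C(90,k)

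This gives 100% for k = 1, 32.6% for k = 2 and 10.4% for k = 3. Summed over k, the expected number is 3 × 30/61 = 1.48.

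**2. Assignments made with at least one arm exhausted.** The k-th assignment from the end is of this kind when the last k envelopes hold at most two arms:

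P(k) = 3 × C(60,k)/C(90,k) − 3 × C(30,k)/C(90,k)

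Summed over k: 3 × 60/31 − 1.48 = 5.81 − 1.48 = 4.33. This total already includes the 1.48 certain ones.

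**3. Correct guesses.** The best strategy names the arm with most envelopes left, which is right with probability (largest remaining count) / (envelopes remaining). Averaged over simulated shuffles:

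| | Tally, 30/30/30 pool | Chance |
|---|---|---|
| All 90 | 36.8 (40.9%) | 30 |
| Last 15 | 8.3 | 5 |
| Last 10 | about 60% | 33.3% |
| Final one | 100% | 33.3% |

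**4. Dependence on the pool being exactly 90.** The same sums, leaving out the envelopes never opened:

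| Pool and stopping point | Expected certain | Expected with an arm exhausted |
|---|---|---|
| 90 envelopes, stop at 90 | 1.48 | 4.33 |
| 96 envelopes (32 per arm), stop at 90 | 0.001 | 0.43 |
| 90 envelopes, stop at 80 | below 0.001 | 0.06 |

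A small surplus or a shortfall in recruitment therefore all but removes the certain tail. With 96 envelopes, 35.1 of 90 can still be guessed if the composition is known.

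**5. How large a bias could follow.** As an assumed stress test, let every participant enrolled when there is a unique best guess be selected 0.5 SD higher if VR is expected and 0.5 SD lower otherwise. The simulated VR-minus-waitlist bias is about 0.10 SD, or about 0.05 SD if steering is limited to the last 15. Both are extreme, since they need steering at every opportunity.

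**6. The alternative: 90 drawn from 120 (40 per arm).** Even if the total became known, 33.2 of 90 are guessable, 6.0 of the last 15, the final one about 40% of the time, and none is certain in practice. The stress-test bias falls to about 0.07 SD. The variance of an arm size is 90 × (1/3) × (2/3) × (30/119) = 5.04, so the SD is 2.2. The variance of an arm difference rises by about 5.04/30² = 0.56%.

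**7. Small fixed blocks.** If the block size were known, the share guessed correctly would be 61% for size 3, 56% for size 6 and 53% for size 9, against 41% for the single pool of 90.

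**The case against.** Numbered, opaque, sealed envelopes opened only after consent are a recognised concealment method, and the gain from counting is 6.8 guesses in 90. The pool is described as about 90, so the certain tail may not arise. Nothing says that the RA who opens envelopes also screens or chooses caregivers. Outcomes are measured at baseline and modelled by group and time, which absorbs part of any selection on initial distress. All of this stands, and it keeps the point minor. It does not remove it: a surplus protects only if it is planned and undisclosed, and the protocol states neither.

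A reader might infer more than the text supports:

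- **That the trial is fully open.** It is labelled single-blinded and the post-test RA is blinded. What is unblinded is the participants and the RA who opens the envelopes.
- **That the shuffle leaves long runs of one arm.** The protocol says only that the envelopes are shuffled. Any run rate would depend on an invented shuffling method.
- **That the PA has a conflict because of** "mass email to participants in a community service project (n>500) for which the PA serves as project manager". The PA prepares the envelopes but is not said to open them or keep a tally, and a mass email cannot be aimed at the next arm.
- **That open recruitment falls at the predictable end.** It is a contingent channel, with no stated place in the sequence.
- **That nothing can show the envelopes were used in order.** The serial numbers allow that check. What cannot be checked is whether the contents match a pre-specified sequence, because none is described.

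**Conclusion.** The point holds as a minor, inexpensive improvement. The protocol itself fixes the method, so this is not a detail left to a later document: a closed pool in thirds, sized to the target, opened serially by someone who sees each result, with concealment claimed only from participants.

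If the pool is 90, all are used and a tally is kept, the excess predictability is about 6.8 guesses in 90, nearly half of it (8.3 − 5 = 3.3) in the last 15. Whether this would turn into bias depends on the enrolling staff having both a tally and some influence over who enters, which the protocol neither states nor rules out. Even extreme steering gives about 0.05 to 0.10 SD. The documents do not show that allocation will be subverted or that the trial's results would be unreliable.

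**What to change.** In the Randomisation section:

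1. Keep the numbered, opaque, sealed envelopes, but fill them in the order of a computer-generated random list. The list should be prepared and held by an existing team member who does not recruit, enrol or assess.
2. Generate more positions than the target, for example 120 (40 per arm), and stop at 90 participants. Do not give enrolling staff the total or the per-arm count.
3. Reconcile the envelopes used against the list at the end of enrolment.
4. State that the sequence is concealed from enrolling staff as well as participants.
5. Do not use small fixed blocks, which would be easier to predict if their size became known.

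The cost is a short script, about 30 more envelopes and a small amount of one team member's time. Arms would no longer be exactly 30 each (SD about 2.2), so the sample size paragraph should say about 30 per arm. The loss of precision is a little over half a percent in the variance of an arm difference.

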#### **C) Usual care group (Waitlist control group)**

The third group will be the waitlist control group, who will not attend any briefing session or engage in mindfulness-based interventions during the pilot period. Instead, they will receive usual care and services provided by community service centres. No additional or new intervention will be provided to them during the study period. We will provide the VR-based MBI to the waitlist control group participants after they have completed the control period.

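### Allocation envelopes hold arm-specific papers not stated to be matched, and concealment is claimed only toward participants, not toward the staff who handle and open them

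*Protocol*

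**What the plan says.** The protocol's Randomisation section sets out the whole allocation procedure.

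- **Who is kept unaware.** The envelope method is used "to ensure that the allocation sequence is concealed from participants before the group allocation". No other party is named.
- **The envelope.** "The PA will prepare about 90 identical, opaque, sealed A5-sized envelopes, with a unique three-digit serial number on the cover".
- **The filling.** "One-third of the envelopes will contain the action plan for the intervention group, another third the action plan for the audio-based MBI group"; the rest hold the waitlist plan. Then: "The intervention materials will be inserted into the envelopes, which will be sealed, shuffled, and numbered". The materials are not described.
- **The opening.** "Once a participant consents to participate in the study, the RA will open one envelope according to the sequence of the serial number" and then assigns the arm from the plan found inside.

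Other sections bear on the point. Under A) VR-based MBI group, the user manual is introduced and the VR glasses are supplied through a briefing session. Under C) Usual care group, the waitlist arm attends no briefing, and "No additional or new intervention will be provided to them during the study period". Under Blinding, participants are unblinded, and the only RA said to be blinded is the one collecting post-test data.

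**The concern.** Concealment must hold against whoever can influence which caregiver enters next. That is normally the staff who screen, recruit, take consent or handle the envelopes. The participant is seldom in a position to exploit the sequence. The protocol claims protection only for the party who needs it least.

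The packing method adds to this. An opaque envelope stops the contents being read, but it does not stop a difference in bulk being felt. Three different action plans, plus materials of unstated kind and amount, go inside, and nothing says that they are matched or that any arm's envelope is padded.

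If the next arm could be sensed, a caregiver could be brought forward or deferred. Treatment is open and the primary outcomes (DASS-21 and ONS4, section (v) Indicators and targets) are questionnaires, so no later safeguard would repair allocation. Blinding the post-test RA protects measurement, not assignment.

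**Working it through.** **1. The plan's own count.** Three arms of 30 give 3 × 30 = 90, which agrees with about 90 envelopes, one-third per arm. No other figure in the document bears on the point.

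**2. What is stated and what is inferred.**

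| Element | Status in the protocol |
|---|---|
| Action plan for the arm inside each envelope | Stated |
| Intervention materials also inserted | Stated, contents undefined |
| Envelopes identical and opaque | Stated, of the envelope |
| Contents matched for thickness and weight | Not stated |
| Contents differ in bulk by arm | Not stated; plausible |
| Concealment from participants | Stated |
| Concealment from staff | Not stated |
| RA opens in serial order after consent | Stated |
| That RA also recruits or takes consent | Not stated, not excluded |
| Participant tied to an envelope before opening | Not stated |

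**3. What predictability would mean.** The document gives no rate, so these are assumed scenarios for a shuffled deck of 30/30/30. They give the chance of guessing the next arm correctly.

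- *Contents indistinguishable:* 30/90 = 33.3%. If someone counts used envelopes and always names the arm with most left, about 41% (10,000 simulated shuffles). This gain comes from the fixed deck, not from the filling.
- *Only waitlist envelopes recognisable:* 30 are known and the other 60 are guessed at one in two. (30 + 60 × 0.5)/90 = 60/90 = 66.7%, or about 72% with counting (same simulation).
- *All three arms recognisable:* 90/90 = 100%.

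These are guess rates, not biases. Turning them into a bias would need the share of allocations actually steered and the prognostic difference of the caregivers steered. The protocol gives neither.

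**4. Does opening after consent close the gap?** Not by itself. It stops an envelope being opened to look, but someone who can feel the next envelope could still time the approach or the consent discussion. Writing the participant's identity on the sealed envelope creates a record of who was committed to which number before the arm was revealed.

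**The case against.** The strongest reply is that the mechanism is inferred. Every envelope, including the waitlist one, contains an action plan. The sentence on intervention materials may simply describe packing those plans. The user manual and glasses belong to the briefing. The statement that the waitlist arm gets nothing new concerns care in the control period, not envelope contents. The protocol also has real safeguards: the PA, not the RA, prepares the envelopes, they are shuffled after sealing, and they are opened in serial order only after consent.

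Most of this stands, and it rules out stronger readings that a reader might infer:

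- *VR envelopes are thick and waitlist envelopes thin.* Not supported. Any difference is probably a matter of paper, and none is stated.
- *The RA who enrols can feel the next arm.* The protocol says only that the RA opens envelopes after consent.
- *The resulting bias could not be removed in analysis.* Too strong. DASS-21 and ONS4 are measured at baseline (Figure 2), and section (vii) Results analysis lists covariates such as health condition and technology literacy. These would adjust in part; unmeasured traits would remain.
- *A shift of some fraction of an SD.* Any such figure rests on assumed steering rates and prognostic gaps, so it only returns its own assumptions.

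The reply does not dispose of the wording. Even if the materials are only the action plans, three different plans are not said to be matched, and concealment still names participants alone. Labelling the sealed envelope could be left to a working procedure; its absence alone would not be a finding.

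**Conclusion.** The point holds as a gap in the stated concealment procedure. The protocol specifies a filling that leaves the next allocation open to feel or weight unless contents are matched, does not say they are matched, and does not extend concealment to the staff who handle the envelopes.

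It is not a demonstrated failure. Actual foreknowledge would require two things that the document neither states nor excludes: contents that differ perceptibly by arm, and a person handling the envelopes who also influences who is approached or consented. The size of any bias is unknown. The guess rates of 33.3%, 66.7% and 100% only show how much predictability depends on what is inside. The change is worth making because it is nearly free and because selection on unmeasured traits during recruitment could not be fully corrected afterwards.

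**What to change.** Reword the Randomisation section in three respects:

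1. Each envelope holds only one allocation card of uniform size and weight, or else contents stated to be matched for thickness and weight across arms. Action plans and materials are handed over after opening.
2. The sequence is concealed from recruiting and enrolling staff as well as from participants. The same paragraph should say who recruits, who takes consent and who opens the envelopes.
3. The participant ID and date are written on the sealed envelope before it is opened.

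The cost is about 90 identical cards and one reworded paragraph. Sample size, allocation ratio and analysis are unaffected. The change needs to be in place before the first envelope is used.
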